#### Caregiver burden

The Oberst Caregiving Burden Scale (OCBS) [43] is used to measure (1) caregiving tasks and responsibilities, (2) relationships and interpersonal support, (3) lifestyle, (4) emotional and physical health, and (5) overall personal impact of being a caregiver. OCBS is a reliable and valid questionnaire that rates 15 different caregiving tasks of informal caregivers based on perceived time and difficulty of the task (e.g., providing personal and medical care, assisting with ADRDLs, monitoring symptoms, managing patient’s emotions and behaviors, dealing with finances, and coordinating and seeking health services). Each item is scored on a 5-point response scale. In response to time for each task, the caregiver chooses an amount ranging from no time to a great deal of time spent on the task related to caregiving. In response to difficulty for each task, the caregiver chooses a value ranging from not difficult to extremely difficult. Similarly, there is a subscale regarding level of distress associated with each task.

Subscale scores for perceived time, difficulty, and distress will be obtained by summing across the 15 items scored 1 to 5. Thus, subscale scores will have a range of 15–75, with higher values indicating more perceived time, difficulty, and distress with caregiving tasks. Evidence of reliability, content validity, and construct validity for the OCBS were reported in prior studies of ADRD [44–46] and TBI [47] family caregivers and people caring for persons receiving cancer treatment [48–50]. Acceptable internal consistency reliability also has been reported in the context of family caregivers of stroke survivors [51, 52].

#### Depressive and anxiety symptoms

We use the 10-item Center for Epidemiologic Studies Depression Scale (CES-D) [53–55] to determine the impact of the ABC ANSWERS intervention on caregivers’ and veterans’ depression. The CES-D is a 10-item depression scale with a total score ranging from 0 to 30, with higher scores indicating more symptoms of depression and a score ≥ 10 indicating depression [55]. To measure anxiety symptoms, we use the Generalized Anxiety Disorder 7-item scale (GAD-7), which is a 7-item anxiety scale with a total score ranging from 0 to 21 [56]. Both the CES-D and the GAD-7 have good internal consistency and test–retest reliability, as well as convergent, construct, criterion, procedural, and factorial validity for the diagnosis of major depression and general anxiety disorder [56–58]. We have used both instruments in multiple research studies, including our dementia collaborative care trials [2, 4, 10, 25–28, 30, 31, 56, 57].

#### Other measures

In addition to the primary and secondary measures described above, we also will measure caregiver and veteran satisfaction with life [59–62]; caregiver’s emotional and physical health strain, feelings of dyadic strain, and role captivity; and the amount of veteran’s distress experienced due to difficulties experienced in completing ADL [63–66].

### Data collection

Research assistants collect survey data by phone or in person at the VHA and are blinded to which condition participants are assigned. Caregivers and veterans are interviewed separately, and each assessment lasts approximately 35–45 min. Research assistants use protocols followed in prior studies to facilitate veterans’ comprehension and participation [67]. Once the assessments are completed, veterans and their caregivers receive $20 gift cards to compensate them for their time in participating in each study interview. To promote participant retention, research assistants call both members of the study dyad to schedule a convenient time to complete outcome assessments. The research team will attempt to contact participants ten times during the 4-week outcome assessment time frame. If a dyad withdraws from the study before their 12-month duration is over, they will no longer be pursued for outcome data. Any outcome data gathered from the dyad while they were enrolled and active in the study will be used for the analyses.

Research assistants attend a 1-day comprehensive training session lead by the principal investigator (PI) and complete two practice interviews with the PI or a coinvestigator who is observing. Training includes all procedures, questionnaires, and the written manual as a reference guide. Topics covered during the training include human subject protection, secure data management, VHA suicide protocol and informed consent, Health Insurance Portability and Accountability Act (HIPAA; Public Law 104–191) guidelines, confidentiality of responses, techniques for interviewing older adults and individuals with ADRD and TBI, and protocols for interviewer assignments and returning completed interviews. All data assessments are reviewed and verified by a second team member before being finalized in the secure RedCap database that sits behind the VHA firewall. Data safety and monitoring will occur at the monthly investigators group meeting. This group will monitor recruitment, enrollment, data collection, intervention procedures, and participant safety issues such as adverse events and protocol deviations on an ad hoc basis. This is a minimal risk study, and we do not anticipate any study-related serious adverse events. However, we will track all adverse events and will report any serious adverse events to the IRB as a reportable VHA event per VHA policy. At continuing review, the IRB will receive a copy of all adverse events not requiring prompt reporting. PHI will not be shared during data safety and monitoring discussions.

### Analysis plan

Randomization results will be compared with a preplanned randomization schedule to ensure randomization integrity. To verify comparability of the randomized groups, baseline characteristics (age, sex, race, and education level) will be compared between randomized groups for veterans and caregivers separately as well as veterans’ comorbid medical conditions, the Charlson comorbidity index, number of primary care visits, and acute care use during the year prior to enrollment. This analysis will be conducted using analysis of covariance models for continuous variables and the Cochran-Mantel-Hansel statistic for categorical variables while controlling for the stratification variable of primary diagnosis (ADRD or TBI). The distributions of continuous variables will be examined, and transformation or nonparametric methods will be used in cases of violation to the normal distribution assumption. In addition, the frequency distribution will be examined for all categorical variables, and exact inference procedures will be used in cases of zero or small cell size. All analyses will be conducted with SAS 9.4 software (SAS Institute, Cary, NC, USA).

Mixed effects models will be used with longitudinally collected QoL scores from veterans as the dependent variable, and randomization group, time, and interaction between group and time as the independent variables while adjusting for the stratification variable of primary diagnosis (ADRD or TBI) and baseline variables that are found to be different between the two groups. An unstructured variance–covariance matrix will be used in the mixed effects model to adjust for potential correlations among measures obtained from the same individual over time. A significant interaction between group and time would indicate differences in QoL changes over time between the ABC ANSWER and control groups. Linear contrasts will be used to compare the QoL scores at each follow-up time between the two groups. Absent significant interaction, significant main group effects would suggest differences in QoL measures between the two groups across all follow-up times. Parametric estimation and inference procedures for the mixed effects models are conducted using the maximum likelihood approach with robust parametric estimation and inference under many missing data mechanisms [68]. In addition, other covariates will be included in the mixed effects models to determine whether specific family member characteristics (e.g., relationship to veteran, frequency or types of contact, other people living in the household) are associated with QoL changes over time. Similar analysis will be conducted for the outcome of caregiver QoL.

Additionally, a mixed effects model will be conducted with caregiver QoL as the outcome variable and veterans’ QoL measures as an additional independent variable to determine how much of the intervention effect on caregiver QoL is mediated through changes in veterans’ QoL measures. By realigning veteran QoL and caregiver QoL, we can also determine whether any mediation effect from veteran QoL is concurrent or has lagged in time.

Similar linear mixed models will be fit for outcomes of caregiver burden (OCBS) and outcomes collected on both veteran and caregiver: depression (CES-D), anxiety (GAD-7), and dyadic strain (dyadic relationship strain and role captivity). All veteran and caregiver outcomes will be fit with separate models. Linear contrasts obtained from the models will be the differences in mean score between the intervention group and the control group at each follow-up time.

For dyad analyses, we will use the dyadic nature of the study design and assess how caregivers’ outcomes are related to veterans’ measures. We will first explore the degree of concordance between paired veteran–caregiver reports using mixed effects models with concurrent veterans’ measures from the same time points as measures of caregivers. ICCs between veteran and caregiver measures will be calculated to assess the degree of chance-corrected agreement between individual veteran and caregiver outcomes, controlling for within-person correlations over time. Mixed effects models will also be used to explore potential mediation effect of the intervention on caregivers’ outcomes from the effect on veterans’ outcomes. For example, we will examine whether intervention effect on caregiver QoL, burden score, and depressive or anxiety symptoms is mediated by an increase in veterans’ QoL or decreased depressive or anxiety symptoms in the intervention group versus the control group. No interim analyses are planned.

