### Primary outcome measures

Caregiver QoL is the primary outcome measure. Secondary outcome measures include caregiver symptoms of depression, anxiety, and caregiver burden. Additional secondary measures for the trial include veteran QoL and symptoms of depression and anxiety. In addition to the psychosocial outcomes data, several additional types of data addressing the implementation and translation process also are examined. Three follow-up data collection periods occur following the baseline (0 months) data collection: short-term (3 months), intermediate (6 months), and sustained (12 months) periods.

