#### Statistical power

Power estimation was conducted using the GLMPOWER procedure in SAS 9.4 software, which takes into account the repeated measures. Power was estimated under two scenarios for potential intervention effects for the primary outcome of veteran QoL. In the first scenario, we assume an early intervention effect with a 0.3 standard deviation (SD) effect size at 3 months and sustained intervention effects of 0.3 SD at 6 and 12 months. In the second scenario, we assume that the effect of intervention is gradual in a dose–response fashion (i.e., 0.17 SD, 0.34 SD, and 0.68 SD effect sizes at 3, 6, and 12 months, respectively). We further assumed a Toeplitz pattern for the correlation structure with correlations of 0.4 for adjacent measures and 0.2 for measures farther apart. With the total enrollment of 200 veteran–caregiver dyads, we expect 10% loss to follow-up rate due to refusal or death. With 180 veteran–caregiver dyads remaining, both scenarios will have > 80% power to detect an intervention effect from a linear mixed model with type I error set at 0.05. Power will be similar for other aims.

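### Baseline QoL is collected but has no prespecified place in the mixed model, so the follow-up contrasts lose precision and the group main effect may be diluted

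*Protocol article*

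**What the plan says.** - **Visits.** Under Primary outcome measures: "Three follow-up data collection periods occur following the baseline (0 months) data collection". The follow-ups are at 3, 6 and 12 months.
- **Model.** Under Analysis plan, longitudinal QoL is the dependent variable, with "randomization group, time, and interaction between group and time as the independent variables" and an unstructured covariance. It is adjusted for diagnosis stratum and for baseline variables found to differ between arms. Caregiver QoL, the primary outcome, gets a similar analysis, as do the burden, depression, anxiety and strain scales.
- **Baseline comparison.** "baseline characteristics (age, sex, race, and education level) will be compared between randomized groups for veterans and caregivers separately". Veterans' comorbidity, Charlson index and prior health care use are added. QoL is not listed.
- **Reading of the terms.** A significant interaction is read as a difference in QoL change over time. Without one, the group main effect is read as a difference across all follow-up times. The contrasts are differences in mean score at each follow-up.
- **Power.** Under Statistical power: "both scenarios will have > 80% power to detect an intervention effect from a linear mixed model", with 180 dyads and "type I error set at 0.05".

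The article does not say whether the month-0 score is one of the repeated responses. Reading the interaction as change over time suggests that it is.

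**The concern.** The covariates are named, so this is a stated model and not simply a gap. It has a weakness under either way of handling month 0.

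- **Baseline as a response, means unconstrained.** With complete data, each follow-up contrast from a saturated group-by-time model is the raw mean difference, and the baseline score adds nothing to it. The group main effect averages over four visits, at one of which randomisation makes the true difference zero. It is then not the effect across follow-up that the plan says it is.
- **Baseline not a response.** A prognostic measure that has already been collected goes unused unless it happens to look imbalanced, which is a data-dependent rule.

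At stake are power in a trial of modest size, exposure of the estimate to chance imbalance in baseline QoL, and a main effect that may be pulled toward zero.

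**Working it through.** **Inputs from Statistical power and study design.** Allocation is 1:1, with 200 dyads enrolled (100 per arm) and 180 analysed (n = 90 per arm). Correlation is 0.4 between adjacent visits and 0.2 between visits farther apart. Scenario 1 is "0.3 standard deviation (SD) effect size at 3 months" and "sustained intervention effects of 0.3 SD at 6 and 12 months". Scenario 2 is "0.17 SD, 0.34 SD, and 0.68 SD effect sizes at 3, 6, and 12 months, respectively". These are stated for veteran QoL, and the article says power is similar for other aims.

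**Assumptions made here.** The test is two-sided, data on the 180 dyads are complete, and baseline is the first of the four correlated measures. Its correlations with months 3, 6 and 12 are then r = (0.4, 0.2, 0.2).

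**Formula.** For a contrast with true value d and variance factor v (SD = 1), the noncentrality is λ = n·d²/(2v). Power comes from the noncentral F with 1 and 178 degrees of freedom.

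**1. The plan's figure (above 80% in both scenarios).**

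| Test, 90 per arm | Scenario 1 | Scenario 2 |
|---|---|---|
| Average of 3 follow-ups, unadjusted | 76.6% | 94.4% |
| Main effect over 4 visits | 58.6% | 82.1% |
| Interaction, 4 visits | 36.8% | 87.5% |

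Scenario 2 is reproduced. Scenario 1 is not, for the model as written. It passes 80% with all 200 dyads (80.8%), with a one-sided test (about 85%), or with baseline adjustment (82.0%, step 2). The article does not say which test was powered, so this is supporting evidence only.

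**2. Average of the three follow-ups, scenario 1.**

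- Unadjusted: v = [3 + 2(0.4 + 0.4 + 0.2)]/9 = 5/9 = 0.5556; λ = 90 × 0.09/(2 × 0.5556) = 7.29; power 76.6%.
- Adjusted: the covariance becomes R − rr′. The mean of r is 0.8/3 = 0.2667, so v = 0.5556 − 0.2667² = 0.4844; λ = 8.36; power 82.0%.
- Variance reduction: 1 − 0.4844/0.5556 = 12.8%.
- Scenario 2 (average effect 1.19/3 = 0.397 SD): 94.4% rises to 96.7%.

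**3. The 12-month contrast, 0.3 SD.** v falls from 1 to 1 − 0.2² = 0.96, λ rises from 4.05 to 4.22, and power from 51.7% to 53.3%.

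**4. Sensitivity to the correlation.** Here a single correlation q between all visits is an assumption; the documents give only 0.4 and 0.2. For the average, v = (1 + 2q)/3 unadjusted and (1 + 2q)/3 − q² adjusted. At 12 months, v = 1 and 1 − q².

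| q | Average: unadjusted → adjusted | 12 months: unadjusted → adjusted |
|---|---|---|
| 0.2 | 83.4% → 86.5% | 51.7% → 53.3% |
| 0.4 | 73.4% → 85.5% | 51.7% → 58.9% |
| 0.6 | 64.7% → 90.6% | 51.7% → 70.6% |
| 0.7 | 60.9% → 94.9% | 51.7% → 80.0% |

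**5. Dilution if baseline is a response.** Scenario 1 main effect: (0 + 0.3 + 0.3 + 0.3)/4 = 0.225 SD. v = [4 + 2(3 × 0.4 + 3 × 0.2)]/16 = 0.475; λ = 90 × 0.225²/(2 × 0.475) = 4.80; power 58.6%. If the interaction is dropped, the generalised least squares weights are 0.286, 0.214, 0.214 and 0.286, the estimate is 0.214 SD and power is about 55%. Scenario 2 falls from 0.397 to 0.298 SD. In scenario 1 the interaction is real but is missed about 63% of the time (100 − 36.8), and the plan then falls back on this diluted main effect.

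**6. Chance imbalance.** At 100 per arm the standard error of the baseline difference is √(2/100) = 0.1414 SD. The chance of a difference above 0.2 SD in either direction is 2[1 − Φ(0.2/0.1414)] = 0.157. Such an imbalance shifts the unadjusted follow-up average by 0.2 × 0.2667 = 0.053 SD on expectation, or 18% of the 0.3 SD target. At 12 months the shift is 0.2 × 0.2 = 0.04 SD.

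**The case against.** The strongest reply is that a condensed article need not say how baseline is coded, and that nothing in it rules out a baseline covariate. The plan's wording places the main effect across follow-up times, which the article defines as 3, 6 and 12 months. Dilution would then arise only if the analysis coded four time levels against that wording. The two harms also belong to different models: if baseline is a response, it does inform the interaction test and helps where follow-up is missing. Baseline QoL could still enter through the rule on variables that differ. Finally, the hypotheses are set at 12 months, where the plan's own correlation yields only a 4% variance reduction.

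Much of this stands as a limit on size. The dilution is conditional, the 12-month gain is small at a correlation of 0.2, and the larger gains rest on assumed correlations. It does not remove the point. The article lists the model's terms and baseline QoL is not among them. A rule triggered by observed differences is not prespecified adjustment and could miss a 0.2 SD imbalance. With baseline as a response, the interaction test uses it but the follow-up contrasts gain nothing from it when data are complete. The plan's reading of the interaction as change over time points toward four time levels, which is at odds with its reading of the main effect.

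**Conclusion.** The concern holds. The analysis is valid, because unadjusted randomised contrasts at each follow-up are unbiased. The avoidable loss for the follow-up average is 12.8% of variance, or 76.6% against 82.0% power in scenario 1. At 12 months it is 4% of variance under the plan's correlation, rising to 49% if the correlation with baseline were 0.7. If month 0 is a time level, the main effect targets 0.225 SD where the follow-up effect is 0.30 SD, with 58.6% power. These figures assume a two-sided 5% test, 90 complete dyads per arm, and baseline sharing the plan's correlation pattern. This should be changed, but it does not put the trial's conclusions in doubt.

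**What to change.** Prespecify one of two models, for caregiver QoL and for every secondary scale measured at baseline:

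- a constrained longitudinal model with all four visits as responses and a common baseline mean in both arms, so that no group effect is fitted at month 0; or
- a mixed model for repeated measures on months 3, 6 and 12, with baseline score and baseline-by-visit as covariates.

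The two give nearly the same precision. State that any overall group effect is the average over months 3, 6 and 12 only, and estimate it by an explicit contrast and not by the main-effect test. Adjustment for the baseline score should not depend on whether the arms are observed to differ.

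The cost is a few lines of analysis plan text and SAS code. No new data are needed, since baseline is already collected. The change should be fixed before unblinding.

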Although the efficacy of interventions for caregivers has been well studied and holds promise to reduce caregiver burden, few studies have taken the next steps in testing the optimal strategies of scaling evidence-based interventions and embedding them into existing Veterans Health Administration (VHA) primary care. To fill the translational gap between clinical care in the research setting and real community practice, our research team is conducting a randomized controlled trial, the Aging Brain Care Acquiring New Skills While Enhancing Remaining Strengths (ABC ANSWERS) study, to examine the impact of integrating two evidence-based programs: a macro, systems-based collaborative care intervention (ABC Program) and a micro, strength-based intervention (ANSWERS) [2, 4, 10, 25–32] into one program delivered within primary care. The primary outcome is caregivers’ QoL. Secondary caregiver outcomes include symptoms of depression and anxiety, dyadic strain, and caregiver burden. Secondary veteran outcomes are symptoms of depression and anxiety. We hypothesize that caregivers in dyads randomized to the ABC ANSWERS program will experience higher levels of QoL and lower levels of depressive and anxiety symptoms, dyadic strain, and caregiver burden at 12 months than those receiving usual VHA primary care. Additionally, we hypothesize that veterans randomized to the ABC ANSWERS program will experience higher levels of QoL and lower levels of depressive and anxiety symptoms at 12 months than those receiving usual VHA primary care.

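### The analysis plan reads several tests of caregiver QoL as evidence of a group difference and names none as primary, so the stated 5% error rate becomes about 6–8%, 10% or up to 16–17%, depending on the reading

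*Protocol article*

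**What the plan says.** The Analysis plan section describes a mixed model for longitudinal QoL with group, time and their interaction. It then explains how the results will be read:

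- Interaction: "A significant interaction between group and time would indicate differences in QoL changes over time between the ABC ANSWER and control groups".
- Visit contrasts: "Linear contrasts will be used to compare the QoL scores at each follow-up time between the two groups". There are three follow-up times. No condition for making these comparisons and no multiplicity adjustment is given.
- Main effect: "Absent significant interaction, significant main group effects would suggest differences in QoL measures between the two groups across all follow-up times".

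The text is written for veteran QoL and then carried over: "Similar analysis will be conducted for the outcome of caregiver QoL". Under Primary outcome measures, "Caregiver QoL is the primary outcome measure", with no time point in that definition. The Background hypothesis for caregivers does have one: "higher levels of QoL and lower levels of depressive and anxiety symptoms, dyadic strain, and caregiver burden at 12 months". The abstract's Discussion paragraph says the same.

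The Statistical power section states that "both scenarios will have > 80% power to detect an intervention effect from a linear mixed model with type I error set at 0.05". It does not say which effect is meant.

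**The concern.** The article gives three ways of finding a group difference on the primary outcome, and one is chosen by a pre-test on the same data. The significance level of 0.05 belongs to no particular test. If each test is run at 0.05 and more than one can support a conclusion, the overall rate exceeds 5%.

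Three consequences follow.

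- **Error rate.** The stated type I error does not describe the conclusion on the primary outcome.
- **Estimand.** The quantity reported (differing change over time, an average, or one visit) depends on the interaction p-value. The hypothesis is about one fixed quantity, the 12-month difference.
- **Power.** The candidate tests have very different power under the plan's own scenarios, so the statement of more than 80% cannot be attached to the primary analysis until the test is named.

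**Working it through.** **Inputs from the article.** 200 dyads, 1:1, 10% loss, so 180 analysed (90 per arm). Correlation 0.4 between adjacent measures and 0.2 between those farther apart. Effects in SD units: scenario 1 is 0.3 at all three follow-ups; scenario 2 is 0.17, 0.34 and 0.68. Type I error 0.05. Assumptions: two-sided tests, each at 0.05, complete data on the 180. The article works out power for veteran QoL and says power is similar for the other aims; the figures are carried to caregiver QoL on that basis.

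**Step 1: reproduce the stated power.** The SE of a difference at one visit is √(2/90) = 0.149 SD.

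- *12-month contrast, scenario 1:* 0.3/0.149 = 2.01, power 51.7%. Baseline adjustment multiplies the variance by 1 − 0.2² = 0.96, giving 53.3%.
- *Average of three follow-ups:* variance (3 + 2(0.4 + 0.4 + 0.2))/9 = 0.556, SE = √0.556 × 0.149 = 0.111. Scenario 1: 0.3/0.111 = 2.70, power 76.6%.
- *The same, adjusted for baseline:* the mean correlation with baseline is (0.4 + 0.2 + 0.2)/3 = 0.267, so the variance is 0.556 − 0.267² = 0.484 and the SE is 0.104. Scenario 1: 0.3/0.104 = 2.89, power 82.0%. Scenario 2: the mean effect is (0.17 + 0.34 + 0.68)/3 = 0.397, power 96.7%.

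Powers are from the noncentral F with 178 denominator degrees of freedom.

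| Test | Scenario 1 | Scenario 2 |
|---|---|---|
| Follow-up average, baseline-adjusted | 82.0% | 96.7% |
| Follow-up average, unadjusted | 76.6% | 94.4% |
| Interaction, baseline as a response (3 df) | 36.8% | 87.6% |
| Interaction, follow-ups only (2 df) | 5.0% | 69.3% |
| 12-month contrast, unadjusted | 51.7% | 99.5% |
| 12-month contrast, baseline-adjusted | 53.3% | 99.6% |

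The stated figure of more than 80% in both scenarios is thus reproduced by the baseline-adjusted follow-up average, and by none of the other tests in the table.

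**Step 2: false-positive rate.** 1,000,000 null draws of the visit differences were made with the article's correlations. Each test was run at 0.05 and the combined rejections were counted under each reading.

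| Reading | Two-sided rate |
|---|---|
| After a significant interaction only the 12-month contrast counts; otherwise the main effect | 5.8% |
| After a significant interaction any visit contrast counts; otherwise the main effect | 7.5–7.9% |
| Interaction or, failing that, main effect | 9.5–9.8% |
| Any of the three visit contrasts | 13.3–13.6% |
| Any route | 16.1–16.8% |

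Ranges cover the model forms tried (baseline as a response, follow-ups only, baseline-adjusted). As a check on the third row, two independent tests give 1 − 0.95² = 9.75%. With an assumed exchangeable correlation of 0.5 or 0.7 in place of the article's, the any-route figure is 14.5–16.2%.

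**Step 3: direction.** Counting only false claims of benefit, a positive main effect or any positive visit contrast occurs in about 7.1–7.3% of null trials. Under the reading in which contrasts follow only a significant interaction, the figure is 3.8–3.9%. One two-sided 0.05 test allows 2.5%.

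**The case against.** The strongest reply is that the section explains what each model term means and does not define success. The verbs are tentative (a result would indicate, or would suggest), and nowhere does the article say that any one significant test makes the trial positive. This stands. A reader might infer from the text that the false-positive rate simply is 10–17%, but the documents do not support that: it requires each route to be taken as sufficient by itself.

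The order of the sentences also allows a familiar reading, in which the contrasts locate a significant interaction and the main effect is read otherwise. The article does not state that condition, but the reading is natural, and the rate is then about 6–8%. The inflation shrinks but does not vanish.

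Two-sided rates also count adverse differences, which could not confirm a directional hypothesis. That is fair, and the benefit-only rates are lower, but they still exceed 2.5%.

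A reader might also infer that the 12-month comparison is missing, or that the interaction has no power against a constant effect. Neither holds as stated. The 12-month contrast is among those planned; only its designation as primary is absent. The interaction has no power in scenario 1 only if baseline is excluded from the responses, which the article does not say; with baseline included its power is 36.8%, and the main effect is there for that case.

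Finally, a separate analysis plan, not shown, may name the test, and an article may leave hierarchy to it. Silence alone would not be a finding. This article, however, sets out a pre-test sequence for the primary outcome beside an error rate of 0.05, and followed as written the sequence does not hold that rate.

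**Conclusion.** The point holds in conditional form. The article gives several readings of a group difference in caregiver QoL, chooses between some of them by a pre-test, and does not make the hypothesised 12-month difference the primary test. The two-sided false-positive rate is about 6–8%, about 10% or up to 16–17% according to how the sequence is read. No reading examined gives 5%. These figures rest on the article's correlations, 90 per arm, complete data and each test at 0.05.

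The choice of test also decides whether the power statement is true: in scenario 1, power runs from about 52–53% for the 12-month contrast to 82% for the baseline-adjusted follow-up average. The matter should be settled before any unblinded analysis because it governs the primary conclusion.

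**What to change.** Delete the rule that turns to the main effect when the interaction is not significant. Name one primary test for caregiver QoL at two-sided 0.05, and report the interaction and all other contrasts as secondary whatever the interaction p-value. Either choice below restores 5%:

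1. **Baseline-adjusted difference at 12 months.** This matches the stated hypothesis. Power must be restated as about 52–53% in scenario 1 and over 99% in scenario 2.
2. **Baseline-adjusted average difference over follow-up.** This fits the power section better (about 82% and 97%), but the hypothesis must be reworded from 12 months to the average over follow-up.

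The power section should name the chosen test. The change is one of wording in the protocol and analysis plan. The cost is fewer routes to a positive claim and, under the first option, a much lower stated power if the effect is constant at 0.3 SD. If an existing analysis plan already names one test, the published text should be brought into line with it.
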